# Effective Primary Prevention of Atopic Dermatitis in High-Risk Neonates via Moisturizer Application: Protocol for a Randomized, Blinded, Parallel, Three-Group, Phase II Trial (PAF Study)

**DOI:** 10.3389/falgy.2022.862620

**Published:** 2022-04-04

**Keywords:** atopic dermatitis, moisturizer, neonate, randomized, controlled trial

## Abstract

**Background:**

Atopic dermatitis (AD) is a chronic and inflammatory skin disease that causes health-related burdens associated with pruritus and poor quality of life. Our previous study demonstrated that moisturizer (2e) application has a primary preventive effect on AD. However, this effect was not observed in recent randomized control trials. Thus, the ideal moisturizer type and application frequency for preventing AD development in infants remains unclear. We hypothesize that twice daily application of moisturizer is more effective than once daily application. We predict that applying sufficient amounts of high-quality moisturizer may be effective for preventing AD development in neonates and infants. Here, we describe a protocol for comparing the efficacy of twice daily and once daily application of Fam's Baby™ moisturizer and once daily application of 2e moisturizer for preventing AD in neonates.

**Methods:**

This study is a single-center, three-parallel group, assessor-blind, superiority, individually randomized, controlled, phase II trial. Sixty newborns with at least one parent or sibling who has had AD is randomly assigned to application of Fam's Baby twice daily, Fam's Baby once daily, or 2e once daily in a 1:1:1 ratio until 32 weeks old. The primary outcome is the time to the first onset of AD during administration of the moisturizer.

**Discussion:**

This is the first phase II randomized, controlled trial in Japan to estimate how effective the twice daily or once daily application of Fam's Baby moisturizer is in preventing AD compared to the once daily application of 2e moisturizer. In this study, we will use 2e once daily as a control to confirm the efficacy for primary prevention of AD as found in our previous trial. Based on the results of this study, we hope to conduct a phase III study to determine the optimal method for preventing AD via moisturizer application. Evaluation of application of moisturizers for preventing AD in this study is expected to contribute to a reduction in the prevalence of AD and a reduction in health care costs.

**Trial registration:**

Japan Registry of Clinical Trials (jRCT); ID: jRCTs031200070.

## Introduction

### Background and Rationale

Atopic dermatitis (AD) is a chronic and inflammatory skin disease that commonly affects young children. AD causes health-related burdens associated with pruritus and poor quality of life (1). A systematic review and meta-analysis showed that parental history of AD increased the risk of AD in the offspring [pooled odds ratio: 3.30, 95% confidence interval (CI): 2.45–4.42] (2). Genetically susceptible individuals have a higher risk of developing AD.

According to a global epidemiological study conducted between 1994 and 1996, the prevalence of AD as reported by parents in a questionnaire was ~7% among school-age children (3). The prevalence of AD as confirmed by a physician's examination in Japan is 12.8% in children aged 4 months old, 9.8% at 1.5 years old, and 13.2% at 3 years old (1, 4). In a previous cohort study involving 1,157 children in Tokyo, Japan, 32.3% of children were diagnosed with AD by age nine, and four AD phenotypes were identified (5).

The possibility of percutaneous sensitization via inflammatory skin of AD is established on the basis of Lack's dual-allergen-exposure hypothesis (6). We found that early-onset infant AD was positively associated with later food allergy in a prospective cohort study (7). AD is considered as an origin of atopic march and the first history of atopic manifestations in children (8). Therefore, whether skin care intervention from an earlier stage of life is effective for primary prevention of allergic diseases, such as AD and food allergies, would be interesting to determine in the future.

In 2014, we performed a randomized, controlled trial (RCT) to evaluate whether moisturizer (2e, Shiseido Japan Co., Ltd., Tokyo, Japan) once daily prevents the incidence of AD at 32 weeks of age compared with a control group in which Vaseline was applied as required from birth (9). This study was a definitive trial, and 118 neonates participated showed that the cumulative incidence of AD was significantly lower in the 2e application group compared with the control group (hazard ratio: 0.48, 95% CI: 0.27–0.86). Recently, Chalmers et al. (10) reported that application of the moisturizer Doublebase Gel (Dermal Laboratories, Herts, UK) or Diprobase Cream (Bayer, Berks, UK) at least once daily had no preventive effect on AD (adjusted relative risk: 0.95; 95% CI: 0.78–1.16; *p* = 0.61). Similarly, Skjerven et al. (11) conducted a study (2 × 2 factorial design) testing two primary prevention strategies (skin care and early food introduction) and showed that an oil bath and application of a moisturizer to the infant's face (Ceridal cream) at least 5 days per week from 0.5 to 9 months of age was not effective in preventing AD. Therefore, unfortunately, these two large RCTs could not confirm the efficacy of moisturizer application for primary prevention of AD. We speculated that these inconsistent findings might be due to different countries and cultures, different moisturizer types, and inadequate adherence in the two large RCTs compared to the previous RCT that reported a preventive effect. The application of high-quality moisturizers in sufficient amounts may effectively prevent the onset of AD in newborns and infants. The efficacy of applying moisturizer is inconsistent regarding primary prevention of AD based on data from previous RCTs. Therefore, the most effective moisturizer type and application frequency for preventing AD development in infants remains unclear.

Fam's Baby (Fam's Inc., Tokyo, Japan) is a popular commercially available moisturizer in Japan. Fam's Baby contains glycerin, stearic acid, dimethicone, liquefied petroleum gas, polyvinylpyrrolidone, triethanolamine, cetanol, caprylic/capric triglyceride, laureth-2, laureth-21, tocopheryl acetate, and phenoxyethanol. Fam's Baby was demonstrated to protect the skin from allergens in a mouse model (unpublished in-house data). In addition, many consumers who used Fam's Baby commented that the skin is maintained in good condition when using Fam's Baby. We hypothesize that twice daily moisturizer application using Fam's Baby is more effective than once daily application and that a sufficient amount and qualities of moisturizer application is effective for preventing development of AD in neonates and infants.

### Objectives

This study aimed to estimate how effective the twice daily or once daily application of Fam's Baby moisturizer is in preventing AD compared to the once daily application of 2e moisturizer.

### Trial Design

This study is a single-center, pragmatic, three-parallel group (1:1:1), assessor-blind, superiority, individually, randomized, controlled, phase II trial (Figure 1).

**Figure 1 F1:**
[figure not shown]
Trial scheme. Newborns with at least one parent or sibling who has had atopic dermatitis will be recruited and enrolled. Participants will be assigned 1:1:1 to groups A, B, and C, and evaluated if they have AD at 4, 12, 24, and 32 weeks for each group.

## Methods

### Study Setting

This study will recruit neonates in the National Children's Hospital (National Center for Child Health and Development [NCCHD], Tokyo, Japan).

### Eligibility Criteria

Neonates with a high-risk of developing AD (*N* = 60) who meet all of the following inclusion criteria and none of the exclusion criteria will be enrolled in this study. Physicians will check if parents or siblings have a history of AD based on the self-report.

### Inclusion Criteria

Neonates must meet the following inclusion criteria to be enrolled in the study:

Newborns aged younger than 6 days old at recruitmentNewborns with at least one parent or sibling who has a past history of AD (high-risk newborn)Newborns whose parents provide written informed consent after receiving an explanation

### Exclusion Criteria

The following exclusion criteria will be used for the study:

Newborns using topical medications, such as steroids (excluding the mouth and anal areas)Newborns with skin lesions, such as abnormal keratinization and bullous diseaseNewborns who are born at <37 weeks in gestationNewborns who are born by cesarean sectionMultiple births (not singletons)Newborns with serious complications that require long-term hospitalization (e.g., heart malformations, respiratory disorders that require intubation)Newborns whose immediate family plans to move and who may not be able to visit the study siteParents unable to understand JapanesePhysicians decide that the neonate is not appropriate for participation in the study

### Interventions

Study physicians will provide guidance to the legal representative (parents) or their family members on how to bathe, how to apply moisturizer, and how to write a diary at the enrollment. These physicians will check the status of entries in the diary for each visit. Participants will be instructed to keep a daily diary to record moisturizer applications, baths, use of combination therapies, occurrence and appearance of rashes, and adverse events. We will instruct not to apply a moisturizer on the visitation day to ensure that the stratum corneum hydration is not affected.

### Intervention in Each Group

Group A: Fam's Baby applied twice a day• Application site: the whole body, except for the scalp• Amount used once: size of a ping-pong ball (0.7 g/piece) with a total of six pieces (total of 4.2 g)• Number of applications: twice a day (of the two applications, one was applied after bathing)• Application period: until 32 weeks of age

2. Group B: Fam's Baby applied once a day• Application site: the whole body, except for the scalp• Amount used once: size of a ping-pong ball (0.7 g/piece) with a total of six pieces (total of 4.2 g)• Number of applications: once a day after bathing• Application period: until 32 weeks of age

3. Group C: 2e applied once a day (9)• Application site: the whole body except for the scalp• Amount used once: one teaspoonful (4.0 g)• Number of applications: once a day after bathing• Application period: until 32 weeks of age

### Intervention and Control Groups

The control group, Group C, will apply 2e moisturizer once a day. In our previous RCT, 2e was shown to prevent AD in neonates with a high-risk of developing AD (9). Based on those findings, we recommend moisturizers for this purpose in clinical practice. The efficacy of Fam's Baby moisturizer for preventing AD development has not yet been evaluated but is expected to have a preventive effect. We considered including a group without moisturizer application as a control; however, we recommend moisturizer application as best practice for neonate skincare. Thus, we determined that including a control group without moisturizers is ethically unacceptable and may interfere with recruitment.

### Criteria for Discontinuing or Modifying Allocated Interventions

Study physicians will discontinue the intervention if the research cannot be continued for the following reasons:

When AD is diagnosedParents request to withdraw the neonate from the study or consent is withdrawnWhen the inclusion criteria are not met or the exclusion criteria are violated after registrationWhen the intervention is difficult to continue because of illness, etc.When participants do not come to the study site owing to movingDiscontinuation of the study is deemed appropriate by the study physicians

Study physicians will consider whether to continue the study in the following cases:

When important information regarding the quality, safety, and efficacy of the intervention is obtainedWhen completing the study is determined as difficult to complete owing to difficulty in recruiting study participants or frequent dropoutsWhen accepting the intervention is determined as difficult because there is an instruction to change the study plan by the independent data monitoring committee or by the Certified Clinical Research Review Committee

### Strategies to Improve Adherence to Interventions

When recruiting participants, if participants are assigned to groups B and C, we will carefully explain to them that they could not apply the moisturizer more than once, and we will also obtain their consents. We will also give the participants approximately the required amount of moisturizer for each visit, and the amount of moisturizer actually used will be calculated by collecting a container of moisturizer at each visit and by measuring the remaining amount, and the frequency of intervention will be confirmed from the diary written by the parents.

### Relevant Concomitant Care Permitted or Prohibited During the Trial

Once a day, the whole body will be washed with soap at the out of bathtub and the soap will be rinsed with water. We will distribute soap to all participants to ensure that the same soap is used.Bath additives will not be used.During the study period, applying other moisturizers, skin topical medicines, and skin application agents is prohibited (excluding the mouth and anal areas).If a skin rash that is not AD appears, physicians will judge whether application of the moisturizer should be interrupted or stopped, and the physicians will start treatment for the skin rash as necessary. If the study intervention is discontinued and treatment improves the condition of the skin, intervention will be resumed. Physicians will record the diagnosis, details of the treatment, and treatment period in an electronic medical chart.When AD is diagnosed, the intervention will be stopped and physicians will carry out appropriate treatment.

### Provisions for Post-trial Care

In case of discontinuation due to illness, we will follow-up participants as long as possible until the situation is restored. If a health issue occurs because of this study, standard treatment will be performed.

### Primary Outcome

Participants will be evaluated for AD at each follow-up visit at 4, 12, 24, and 32 weeks after birth. The primary outcome is the time to the first onset of AD during application of the moisturizer. The time to onset of AD is defined as the number of days between discharge of the newborn and the onset of AD. The UK Working Party's diagnostic criteria (12) will be used as diagnostic criteria of AD.

### Secondary Outcomes

Efficacy endpoints include the following: (1) Eczema Area and Severity Index (EASI) scores (13) at 4, 12, 24, and 32 weeks after birth; (2) patient-oriented eczema measure (POEM) scores (14) during the study; (3) stratum corneum hydration at the date of registration at 4, 12, 24, and 32 weeks after birth; (4) total immunoglobulin E (IgE) antibody titer and specific IgE antibody titer (ImmunoCAP) at the diagnosis of AD or at 32 weeks after birth; and (5) serum thymus and activation-regulated chemokine levels at diagnosis of AD or at 32 weeks after birth (15).

### Safety Outcomes

Safety outcomes describe the frequency and proportion of adverse events.

### Adverse Event Reporting and Harms

In this study, any adverse events that occur during the study intervention period (after discharge) will be investigated, and the investigators will report the following items to the data center: (1) event name; (2) date of onset; (3) severity (mild, moderate, and severe); (4) seriousness (serious, non-serious); (5) intervention measures (continuation, interruption, and discontinuation); (6) measures [none, yes (contents if yes)]; (7) outcomes (recovery, remission, unrecovered, recovered but with sequelae, death, and unknown) and outcome confirmation date; and 8) causal relationship with moisturizer use (can be denied, cannot be denied).

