### Participants' Timeline

A summary of participants' timeline is shown in Table 1.

**Table 1 T1:** Assessment schedule.

	**Study period**				**Endpoint**	**Unscheduled medical examination (appearance of skin rash, etc.)**	**When the study intervention is discontinued (including when atopic dermatitis is diagnosed)**
**Visit**	**1**	**2**	**3**	**4**	**5**		
**Time point (visit windows)**	**Entry (6 days old)**	**4 weeks after entry (±7 days)**	**12 weeks after entry (±14 days)**	**24 weeks after entry (±28 days)**	**32 weeks after entry (±28 days)**		

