### Statistical Methods

#### Statistical Methods for Outcomes

Analysis will be performed according to the intention-to-treat principle. To assess whether group A or group B is more effective than group C in preventing the onset of AD, we will use two co-primary analyses using the log-rank test for the time to the onset of AD. The significance level of each comparison is 2.5%. For each group, Kaplan–Meier estimates of the AD-free rate will be determined. Additionally, the Cox proportional hazards model will be used to estimate the hazard ratios of groups A vs. C and groups B vs. C, and their 95% CIs. The CIs will be calculated using the Wald type method. The exact method will be applied to adjust for tied observation times. A test with Schoenfeld residuals will be used to assess the proportional hazard assumption. If a significance level of 10% rejects the validity of the proportional hazards assumption, group comparisons using the difference in the restricted mean survival time will be applied as a supplementary analysis of the co-primary analysis. For the secondary endpoints, the mean and standard deviation of continuous variables, and the frequency and proportion of discrete variables will be calculated for each treatment group and time point. For the safety endpoints, the frequency and proportion of adverse events occurring will be calculated for each treatment group.

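### Adverse events are counted over a period that an AD diagnosis appears to end, and are summarised only as crude frequency and proportion, so the safety summary depends on the primary outcome

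*Protocol article*

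**What the plan says.** **Collection window.** Adverse Event Reporting and Harms: "any adverse events that occur during the study intervention period (after discharge) will be investigated". The onset date of each event is among the reported items.

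**What ends the intervention.** Intervention in Each Group sets the planned length: "Application period: until 32 weeks of age". Criteria for Discontinuing or Modifying Allocated Interventions lists an AD diagnosis first among the reasons to stop. Relevant Concomitant Care says the same: "When AD is diagnosed, the intervention will be stopped and physicians will carry out appropriate treatment".

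**Visits.** Table 1 checks adverse events at visits 2 to 5, at unscheduled examinations, and in a column headed "When the study intervention is discontinued (including when atopic dermatitis is diagnosed". No later visit is scheduled for that infant. Provisions for Post-trial Care adds only this: "In case of discontinuation due to illness, we will follow-up participants as long as possible until the situation is restored".

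**Summary measure.** Safety Outcomes: "Safety outcomes describe the frequency and proportion of adverse events". Statistical Methods for Outcomes: "the frequency and proportion of adverse events occurring will be calculated for each treatment group". Neither section uses observation time.

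**Primary outcome.** "The primary outcome is the time to the first onset of AD during application of the moisturizer".

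**The concern.** The event that defines the primary outcome also appears to close the safety window. An infant who stays free of AD is observed for about 32 weeks; one diagnosed at the 4-week visit is observed for about 4. Between groups, average observation time is longer where AD is less frequent or later. A crude count or proportion takes no account of this, so two products with the same true event rate are expected to show different crude figures whenever they differ in preventing AD.

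The article hopes that a phase III trial will follow from these results. In the crude figures, a product that prevents more AD would tend to look slightly less well tolerated, and one that prevents less would tend to look slightly better, for a reason unrelated to harm. The same applies between the two Fam's Baby groups if they differ in AD incidence.

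**Working it through.** **Step 1. Does the window end at AD diagnosis?** The article does not define the study intervention period. Read as a fixed 32 weeks for every infant, the problem would largely go. Four places point the other way:

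- Two sections stop the intervention at diagnosis.
- The discontinuation column of Table 1 names AD diagnosis, and nothing follows it.
- Secondary Outcomes takes IgE and TARC at AD diagnosis or at 32 weeks, which treats diagnosis as that infant's end point.
- The per protocol set applies its 70% adherence rule over the same period. On a fixed 32-week reading, an infant diagnosed before about week 22 (0.7 × 32 = 22.4) would be likely to fail the rule simply by having the primary event.

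**Step 2. Inputs.**

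- From the article: maximum application to 32 weeks of age; 20 infants per group; hazard ratio 0.48 from the sponsor's previous trial (2e against Vaseline as required), given in Background and Rationale.
- Assumed: the 0.48 carries over to a Fam's Baby group against group C; AD incidence in C by 32 weeks, I, is 10% to 50%; the AD hazard is constant; adverse events occur at the same constant rate r in both groups.
- The article has no safety figure to reproduce.

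**Step 3. Formulas.** With S = 1 − I in group C and S = (1 − I)^0.48 in the preventive group, and λ = −ln(S)/32:

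- mean observation = (1 − S)/λ
- expected events in 20 infants = 20 × r × mean observation
- P(at least one event) = r/(r + λ) × (1 − exp(−32(r + λ)))

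The ratio of expected counts is the ratio of mean observation times, whatever r is.

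**Step 4. One case in full, I = 30%, r = 1 event per 32 weeks.**

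- Group C: λ = 0.3567/32 = 0.01115; mean 0.30/0.01115 = 26.9 weeks; events 20 × 26.9/32 = 16.8; at least one event 54.7%.
- Preventive group: S = 0.7^0.48 = 0.843; λ = 0.00535; mean 0.157/0.00535 = 29.4 weeks; events 20 × 29.4/32 = 18.4; at least one event 58.9%.
- Count ratio 1.09, with the true rates equal.

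**Step 5. Over the range of I, hazard ratio 0.48, r = 1 per 32 weeks.**

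| AD in C | AD in preventive group | Weeks, C vs preventive | Events, C vs preventive | At least one event | Count ratio |
|---|---|---|---|---|---|
| 10% | 4.9% | 30.4 vs 31.2 | 19.0 vs 19.5 | 60.5% vs 61.9% | 1.03 |
| 20% | 10.2% | 28.7 vs 30.3 | 17.9 vs 19.0 | 57.7% vs 60.5% | 1.06 |
| 30% | 15.7% | 26.9 vs 29.4 | 16.8 vs 18.4 | 54.7% vs 58.9% | 1.09 |
| 40% | 21.7% | 25.1 vs 28.4 | 15.7 vs 17.7 | 51.6% vs 57.2% | 1.13 |
| 50% | 28.3% | 23.1 vs 27.2 | 14.4 vs 17.0 | 48.2% vs 55.2% | 1.18 |

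**Step 6. Sensitivity.** With hazard ratios from 0.3 to 0.7 the count ratio runs from 1.02 to 1.25. If every AD case were diagnosed at the 4-week visit, at hazard ratio 0.48, it would be 1.17 (I = 30%) or 1.34 (I = 50%).

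**Step 7. Noise.** In the 30% case the expected difference is 18.4 − 16.8 = 1.6 events. Treating counts as Poisson, its standard deviation is about √(18.4 + 16.8) = 5.9. For the proportion, the difference is 4.2 percentage points against a standard error of √(0.589 × 0.411/20 + 0.547 × 0.453/20) = 0.157, or about 16 points.

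**Step 8. If AD is itself counted as an adverse event.** In the 30% case this adds 20 × 0.30 = 6.0 events in C and 20 × 0.157 = 3.1 in the preventive group: 22.8 vs 21.5, ratio 0.94. The article does not say whether AD is counted.

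**Step 9. With person-time.** Events divided by infant-weeks has expected ratio 1.00 when the true rates are equal, provided AD is kept out of the count.

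**The case against.** The strongest case against has five parts.

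- **This belongs in the statistical analysis plan.** Exposure-adjusted reporting is often left there, and the article is a condensed account that plans no safety test. That limits the weight of the point. But the article does state the window, the stopping rule, the visits and the summary measure, and together these give a measure that depends on efficacy. The point does not rest on silence.
- **A reader might infer that collection stops whenever the moisturizer is not being applied.** The article does not say so. Application may be interrupted for a rash that is not AD and then resumed, and nothing ends collection meanwhile. Unscheduled and discontinuation visits also record events. It is the end of the intervention at AD diagnosis that matters.
- **A reader might infer that the better product will show more adverse events in this trial.** That holds only in expectation. Steps 7 and 8 show that chance, or the counting of AD, could hide or reverse it.
- **A reader might expect a much larger excess.** AD incidence of 15% against 50% with mean diagnosis at week 8 gives (0.85 × 32 + 0.15 × 8)/(0.50 × 32 + 0.50 × 8) = 28.4/20 = 1.42. But this implies a hazard ratio of ln 0.85/ln 0.50 = 0.23. The article's 0.48 was against Vaseline as required; here the comparator is 2e itself, so an even stronger effect has no support in the document.
- **Ending collection with the intervention is defensible.** After diagnosis infants receive AD treatment, so events recorded to 32 weeks would include effects of that treatment, more often where AD is more frequent. This objection stands, and it is why longer collection is not part of the required change.

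**Conclusion.** The point holds in a limited form. Read together, the sections make safety observation time depend on the primary outcome, and the stated crude summaries do not allow for it. If the groups differ in AD incidence, the group with less AD is expected to show more non-AD adverse events at the same true rate.

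The size is modest: about 3% to 18% more events for AD incidence of 10% to 50% in group C, at hazard ratio 0.48 and constant hazard, and more if diagnoses cluster early. AD incidence, the effect of Fam's Baby against 2e and the event rates are all assumptions, so only the direction is firm. It also rests on reading the intervention period as ending at AD diagnosis, which the article indicates but does not define.

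The documents do not support saying that the safety results will be misleading, or that a phase III decision rests on this comparison: the article links phase III to the best method of prevention. A better measure is nevertheless available at almost no cost and should be used.

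**What to change.** In Statistical Methods for Outcomes, add to the crude frequency and proportion the number of adverse events per infant-week of observation in each group. Count time from discharge (or start of application) to the end of adverse event collection for that infant, and state which start and end dates are used. Show AD separately from other adverse events. It would help to say in the same place that the study intervention period ends at AD diagnosis, if that is what is meant.

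The cost is a few lines of analysis. Event onset dates are reported, the primary outcome already needs the dates of discharge and AD onset, and the daily diary records applications. The crude figures stay, so nothing is lost.

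Recording adverse events to 32 weeks in infants who have stopped is an optional consideration for the phase III trial. Here it would mix in effects of AD treatment, and it comes largely too late: recruitment was complete by September 2021, so an infant born at the end of that month reaches 32 weeks (224 days) in mid-May 2022, and the article appeared on 4 April 2022.
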